#### Secondary outcomes

This study intends to further assess the effectiveness of CGM-based intraoperative glucose management in LT by mean intraoperative glucose values, as well as rates of hypoglycemic events and hyperglycemic events. The accuracy of CGM for intraoperative glucose monitoring will be evaluated by overall clinical mean relative error and Clarke error grid analysis. The safety of CGM for intraoperative glucose monitoring will be evaluated by the incidence of severe adverse reactions (SAEs).

Additionally, this study intends to evaluate the prognostic improvement of patients with different glucose monitoring modalities by comparing the incidence of SSIs, other infections, postoperative liver function, and major adverse cardiovascular events (MACE) in the two groups at 3 months postoperatively.

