### Statistical methods

#### Statistical methods for primary and secondary outcomes {20a}

Continuous variables such as CV%, mean blood glucose, and liver transaminases levels and other indicators will be tested for normality using Kolmogorov–Smirnov test. Measures satisfying normal distribution will be expressed as mean ± standard deviation, and median (interquartile range) when data are not normally distributed. Qualitative data such as the incidence of hypo/hypoglycemia, SSIs, and MACE will be expressed as frequencies (percentages).

Normally distributed data will be compared between two groups using *t*-test, multiple groups will be compared using ANOVA, and non-normally distributed data will be compared using Mann–Whitney *U*-test. The chi-square test will be used for comparison between groups for numerical data. Comparisons of CV%, the primary outcome, will be made using either the *t*-test or the Mann–Whitney *U* test.

Repeated measures will be compared using analysis of variance (ANOVA). Blood glucose analysis will be performed using multifactorial analysis.

In this study, the accuracy of CGM monitoring will be tested simultaneously for patients in the CG group. Pearson linear correlation analysis will be applied to determine the correlation between CGM- and ABG-derived glucose levels; Clarke error grid analysis will be used to evaluate the consistency between CGM- and ABG-derived glucose levels. The formula: [ABG glucose − CGM glucose)/ABG glucose] × 100% will be applied to calculate the overall clinical mean relative error. If this error value is ≤ 17% and the sum of the data falling in areas A and B in the Clark error grid analysis is not less than 95% of the total, the accuracy will be judged to be satisfactory.

All analyses will be performed using SPSS 26.0 (SPSS, USA) and STATA 14.0 (StataCorp LP, College Station, TX).

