## Discussion

This is a randomized, prospective, unblinded, study evaluating the potential superiority of CGM-based intraoperative glucose management. Low GV in clinical trials indicates improved postoperative outcomes and therefore was chosen as the primary endpoint. Secondary endpoints include mean intraoperative glucose levels and the incidence and extent of both hyperglycemic and hypoglycemic disorders. Furthermore, 3-month follow-up will help us explore whether intraoperative CGM monitoring could reduce the incidence of post-LT infectious events such as SSIs and MACEs and thus improve patients’ prognosis.

To the best of our knowledge, this is the first study investigating the prognostic role of CGM-based intraoperative glucose management in LT. The current study aims to realize continuous dynamic monitoring of intraoperative glucose and clarifies the effectiveness and feasibility of CGM for intraoperative glucose monitoring. Moreover, this study for the first time used GV coefficient as a key indicator of intraoperative glucose management and explored the impact of high GV on postoperative glucose-related complications, in addition to hyperglycemia and hypoglycemia.

This study has the following advantages. First, the study is conducted on liver transplant recipients. Most patients with end-stage liver disease have glucose metabolism disorders, and LT surgery is a traumatic procedure with high intraoperative doses of catecholamines, glucocorticoids, and other drugs that affect glucose metabolism, which leads to a higher incidence of intraoperative glucose disorders in LT recipients than in other procedures and often more severe. The high incidence and severity of glucose disorders help to verify the real-time effectiveness of novel glucose regulation model. Second, the study used arterial blood gas glucose as the gold standard and clinical overall mean relative error and Clarke error grid analysis to assess the accuracy of CGM for intraoperative glucose monitoring. The results of the study are therefore reliable and may be applicable to other major procedures. Finally, this study will be followed up for 3 months after surgery to fully reveal the impact of intraoperative GV and glucose levels on postoperative glucose-related complications.

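### The CGM accuracy limit of 17% is applied to a signed mean, so it bounds bias in one direction rather than the size of error, and the Clarke condition only partly makes up for this

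*Protocol article*

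**What the plan says.** The Secondary outcomes section of the protocol article names device accuracy as an outcome: "The accuracy of CGM for intraoperative glucose monitoring will be evaluated by overall clinical mean relative error and Clarke error grid analysis".

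The section on statistical methods for primary and secondary outcomes {20a} turns this into a pass/fail rule. The check is confined to one arm ("the accuracy of CGM monitoring will be tested simultaneously for patients in the CG group"). The error is defined by the formula "ABG glucose − CGM glucose)/ABG glucose] × 100% will be applied to calculate the overall clinical mean relative error". The rule then reads "If this error value is ≤ 17% and the sum of the data falling in areas A and B" of the Clarke grid "is not less than 95% of the total, the accuracy will be judged to be satisfactory".

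Both conditions must therefore hold. The limit on the error is an upper one, with no lower bound. The Discussion names the same measure ("clinical overall mean relative error and Clarke error grid analysis to assess the accuracy of CGM"). In none of these places is the error called absolute.

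**The concern.** A limit on average error should answer how far, typically, the CGM reading lies from the arterial value. The mean of a signed relative difference answers a different question: whether the device reads high or low on balance. A device with large errors in both directions can score zero. Because the limit is only an upper one and the difference is ABG minus CGM, a device that reads too high on average scores below zero and meets the limit whatever the size of the error.

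At stake is the verdict on a named secondary outcome. The Introduction presents the accuracy of interstitial CGM during surgery as an open question, and the Discussion cites this measure in support of reliable results that may carry over to other major procedures. A prespecified rule that can call a mean absolute error well above 17% satisfactory does not support that use.

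**Working it through.** **Inputs from the protocol article, section {20a}:** error = (ABG − CGM)/ABG × 100%; limit ≤ 17%; Clarke A+B ≥ 95%; both required. The 17% is a set threshold, not a derived figure, so there is nothing to reproduce.

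**Step 1, algebra (no assumptions).** Write CGM = ABG × (1 + e). The printed error of one pair is (ABG − ABG(1 + e))/ABG × 100% = −100e%. Hence:

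- Cancellation: half the pairs at e = +0.30 and half at e = −0.30 give a signed mean of (−30 + 30)/2 = 0%, which meets the limit. The mean absolute error is (30 + 30)/2 = 30%.
- Over-reading: e = +0.20 throughout gives −20%, and e = +1.00 gives −100%. Both are ≤ 17%.
- Asymmetry: e = −0.20 throughout gives +20% and fails, although the error is the same size as the +20% over-reading that passes.

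**Step 2, does the Clarke condition catch these cases?** This needs a glucose distribution and the zone boundaries, which the documents do not give. Assumptions: ABG glucose lognormal with median 9.5 mmol/L and log-SD 0.28; standard Clarke zones; simulated pairs (200,000 or more per case).

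| CGM error pattern | Signed mean (as printed) | Mean absolute error | Clarke A+B | Printed joint rule |
|---|---|---|---|---|
| Half +30%, half −30% | 0% | 30% | 98.0% | passes |
| Mean +20%, SD 5% | −20% | 20% | 100% | passes |
| Mean +30%, SD 10% | −30% | 30% | 98.6% | passes |
| Mean +40%, SD 5% | −40% | 40% | 96.7% | passes |
| Mean +40%, SD 10% | −40% | 40% | 93.3% | fails on Clarke |
| Constant +50% | −50% | 50% | 84.4% | fails on Clarke |
| Mean +60%, SD 5% | −60% | 60% | 62.6% | fails on Clarke |
| Unbiased, SD 25% | about 0% | 19.9% | 97.7% | passes |
| Unbiased, SD 30% | about 0% | 23.8% | 95.5% | passes narrowly |
| Mean −20%, SD 5% | +20% | 20% | 99.6% | fails on the 17% limit |

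Every row would fail a 17% limit on the mean absolute error.

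**Step 3, range over the assumption.** With the median varied from 8.5 to 11.5 mmol/L and the log-SD from 0.2 to 0.4 (12 settings):

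- The ±30% pattern keeps A+B at 95.5% to 99.6%, so it passes throughout.
- A constant +50% over-reading gives 66% to 91% in 11 settings and 96.7% in one, so it usually fails.
- An unbiased normal error with a mean absolute error of 25% gives 90.8% to 97.3% (94.7% at the central setting), so it is borderline.

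**The case against.** Three arguments carry weight.

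- **The verdict is joint.** A reader might infer that any over-reading device would be declared satisfactory. The documents do not support that. Any net over-reading meets the 17% limit, but the overall verdict also needs Clarke A+B ≥ 95%, and that usually rejects a constant +50%. The argument stands for very large errors. It does not stand for the ±30% pattern or for over-reading of 20% to 30%; at about 40% the outcome depends on the spread.
- **The formula may be a misprint.** Its bracket is unbalanced, so at least one symbol was lost or mistyped, and an upper limit alone makes sense only for a non-negative quantity. Absolute-value bars may well have been intended. This limits what can be said about what the trial team will do. It does not remove the need for correction, because an analyst following the text would average signed values.
- **The reach is limited.** A reader might infer that the validity of the primary outcome rests on this verdict. No section makes the CV% analysis depend on it, and proportional over-reading leaves CV% unchanged: (1 + e)SD/((1 + e)mean) = SD/mean. Random device error can affect CV%, but correcting this formula would not alter that. A reader might also infer that the rule lets low glucose go unnoticed in theatre. The rule is applied at analysis and governs no care, and treatment in both groups follows arterial values. Even at +50%, an arterial 3.9 mmol/L displays as 3.9 × 1.5 = 5.85, below both low CGM triggers printed in the protocol (6.1 and 7.8 mmol/L). Those two figures are a separate inconsistency to be reconciled.

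**Conclusion.** The point holds for the accuracy criterion. That the printed formula measures bias, lets errors of opposite sign cancel and accepts any net over-reading within the 17% limit is algebra and needs no assumption. That the joint rule can still return a satisfactory verdict with a mean absolute error of 20% to 30% rests on the assumed glucose distribution and standard Clarke zones. For the ±30% pattern it held in all 12 settings examined. Whether the signed form is deliberate or a misprint cannot be settled from the article. The consequence is confined to a secondary outcome; the primary CV% comparison, the sample size and participant management are unaffected.

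**What to change.** In section {20a}, define the criterion as the mean over pairs of |CGM − ABG|/ABG × 100% and apply the 17% limit to that quantity. Keep the Clarke condition as it stands. Report the mean of the signed difference separately, labelled as bias, with its direction stated. Use the same name for the measure under Secondary outcomes and in the Discussion, including the word absolute. If absolute values were always intended, say so and correct the bracket.

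The change costs one formula and matching wording in two other places, and should be made before the data are analysed. The stated accuracy may look less favourable: a device with unbiased error of SD 25% would be reported at 19.9% and fail, rather than at about 0% and pass.

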#### Interim analyses {21b}

A primary analysis will be conducted for this study and no interim analysis is planned.

#### Methods for additional analyses (e.g., subgroup analyses) {20b}

We will perform subgroup analysis based on the value of HbA1C (≤ 6.5% vs 6.5 ~ 8.5%). “*P*” value < 5% to be considered statistically significant. The differences of outcomes between subgroups will be evaluated using interactive subgroup analysis.

#### Methods in analysis to handle protocol non-adherence and any statistical methods to handle missing data {20c}

All randomized participants will be included in the main analyses. An intention-to-treat analysis will be carried out relating to any protocol non-adherence or dropouts. Per-protocol dataset will also be performed for any of the missing data. Besides, we anticipate little loss to follow-up for the primary outcome. Nevertheless, if there is more than 5% missing data for the primary outcome, we will perform a sensitivity analysis using multiple imputations for the missing data.

#### Plans to give access to the full protocol, participant-level data, and statistical code {31c}

The full protocol is publicly available. The public can obtain de-identified participant-level data and statistical code by reasonable written request to the principal investigator.

### Oversight and monitoring

#### Composition of the coordinating center and trial steering committee {5d}

Being a single-center study, the principal investigator ([name]) and whole team are responsible for patient recruitment, data collection, maintaining the protocol, and patient follow-up. The Data Safety Monitoring Board (DSMB) will frequently monitor the study and report on trial quality control.

#### Composition of the data monitoring committee, its role and reporting structure {21a}

The DSMB is responsible for ensuring the safety of patients participating in the trial. The DSMB consists of three independent individuals, including statisticians and clinical decision makers. The DSMB meets at least once a year. The DSMB declares no competing interests.

#### Adverse event reporting and harms {22}

Treatment-related clinical adverse reactions including puncture site hematoma, infection, hypoglycemia, and hyperglycemia will be considered. The investigator should inform the participant of any emerging adverse events, and the participant should also report changes in condition truthfully in accordance with the protocol. The investigator should keep detailed records of all adverse events, including symptoms, time of presentation, duration, management measures, and effects, and evaluate their relevance to the study treatment. Investigators should be alert for serious adverse events (SAEs) such as severe hypoglycemia (< 3. 0 mmol/L), cardiac arrest due to dysglycemia, or death. Protecting the safety of the participants is the primary responsibility of the investigator. It should also be reported to the ethics committee, data monitoring committee, and relevant regulatory agencies, indicating the expectedness, severity, severity, and causality. DSMA regularly reviews study data and adherence to the protocol and makes recommendations regarding continuation, modification, or termination of the trial when necessary.

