### Interventions

#### Explanation for the choice of comparators {6b}

In this study, blood glucose in the control group will be measured by ABG testing at 2-h intervals, and the monitoring frequency will be adjusted according to the single glucose value, which is the most common way of blood glucose monitoring at present. However, this monitoring method has the disadvantages of not reflecting GV and easily missing the diagnosis of blood glucose disorder. In the intervention group, CGM combined with ABG test will be used for blood glucose monitoring. In brief, ABG test will be performed to verify the blood glucose value when the CGM monitoring value is abnormal (< 7.8 mmol/L or > 10 mmol/L). The blood glucose intervention in both groups will be based on the blood glucose values obtained from ABG test.

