### Intervention description {11a}

#### Blood glucose management

Blood glucose monitoring

Intraoperative glucose monitoring is performed in both groups using CGM (Guardian RealTime, Medtronic, USA) in combination with arterial blood gas. A disposable glucose monitoring probe will be placed in the patient's upper arm by the investigator 6 h before surgery and connected to the monitoring system.

In the CG group, intraoperative ABG testing will be performed if the CGM value is < 6.1 mmol/L or > 10.0 mmol/L, or the rate of change of CGM value > 1.67 mmol/(L·min). Blood glucose adjustment will be performed according to the arterial blood glucose value.

In the G group, CGM monitoring results were blinded to patients and investigators. Intraoperative arterial blood gas checks will be performed every 2 h, and blood glucose adjustments will be made based on blood glucose results, and the frequency of blood gas tests will be adjusted as needed. CGM is used to record intraoperative glucose data only.2)Blood glucose management target: The intraoperative blood glucose management target is 7.8 ~ 10 mmol/L in both groups.3)Blood glucose-lowering measures: see Table 1 for the intraoperative glucose management measures for patients in both groups.

**Table 1 Tab1:** Blood glucose intervention

Perioperative target blood glucose: 7.8 ~ 10 mmol/L • If ABG-derived blood glucose > 10 mmol/L measured for the first time, start insulin infusion Insulin dose and mode of administration: • Loading dose: 0.1 U/kg, I.V Maintenance dose: (blood glucose value/5)U/h, infusion			
**Blood glucose (mmol/L)**	**If BG increased from previous measurement**	**BG decreased from prior measurement by ≤ 1.67 mmol/L**	**BG decreased from prior measurement by > 1.67 mmol/L**
**> 13.4**	Increase rate by 3U/h	Increase rate by 3U/h	No change in rate
**11.7 ~ 13.4**	Increase rate by 2U/h	Increase rate by 2U/h	No change in rate
**10.0 ~ 11.7**	Increase rate by 1U/h	Increase rate by 1U/h	No change in rate
**7.8 ~ 10.0**	No change in rate	No change in rate	No change in rate
**6.1 ~ 7.8**	No change in rate	Decrease rate by 50%	Hold insulin infusion
**5.5 ~ 6.1**	• Hold insulin infusion • Check BG every 2 h • Restart infusion if BG > 10 mmol/L		
**3.9 ~ 5.5**	• Hold insulin infusion • Check BG every 30 min until BG > 5.5 mmol/L, resume BG checks every 2 h • Restart infusion at 1/2 the prior infusion rate if BG > 10 mmol/L		

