### Outcomes {12}

#### Primary outcomes

Intraoperative glucose coefficient of variation. In this study, the intraoperative coefficient of variation of blood glucose will be extracted from the CGM data for each participant (from the beginning of skin incision to the end of suture).

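### Glucose-defined adverse events, including severe hypoglycaemia as an SAE, are detected by different means in the two arms, so comparing their incidence between arms is biased by an amount the protocol cannot fix

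*Protocol article*

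**What the plan says.** Under Adverse event reporting and harms {22}, the protocol article lists dysglycaemia among the adverse reactions: "Treatment-related clinical adverse reactions including puncture site hematoma, infection, hypoglycemia, and hyperglycemia will be considered". It then names a glucose threshold as serious: "Investigators should be alert for serious adverse events (SAEs) such as severe hypoglycemia (< 3. 0 mmol/L". Under Secondary outcomes, "The safety of CGM for intraoperative glucose monitoring will be evaluated by the incidence of severe adverse reactions (SAEs". The same section lists mean intraoperative glucose "as well as rates of hypoglycemic events and hyperglycemic events", without naming the data source.

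Monitoring differs by arm. For CG, Blood glucose management says "intraoperative ABG testing will be performed if the CGM value is < 6.1 mmol/L or > 10.0 mmol/L", or if the rate of change is too high. Section {11c} adds a continuous device alarm, and section {11d} restricts CG blood gas tests to those triggers. For control, "In the G group, CGM monitoring results were blinded to patients and investigators"; ABG is every 2 h, adjusted as needed, and section {11d} discourages shorter intervals without a clear indication. Table 1, which applies to both arms, moves to 30-min checks once a measured value is 3.9 to 5.5 mmol/L or 2.8 to 3.9 mmol/L, and to 15-min checks at 2.8 or below.

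Section {6b} says of the control method that "this monitoring method has the disadvantages of not reflecting GV and easily missing the diagnosis of blood glucose disorder". For the primary outcome a common source is fixed: "the intraoperative coefficient of variation of blood glucose will be extracted from the CGM data for each participant".

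**The concern.** In an anaesthetised patient, hypoglycaemia is found mainly by measuring glucose, and an investigator can record only an episode that some displayed measurement reveals. CG has a visible, alarmed trace plus triggered ABG; G has ABG alone in real time. With equal true rates, the arm that is watched more closely tends to report more events, and a real reduction under CGM could be hidden or reversed.

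At stake are the comparison of hypo- and hyperglycaemic adverse reactions and of glucose-defined SAEs, and with them the safety verdict on CGM. Section {22} also provides for regular data review with recommendations on continuing, modifying or terminating the trial, so an artefact in these counts could reach that review. Blinding the outcome assessors and analysts does not help, because a missed episode is lost before it reaches them.

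**Working it through.** The document gives no event rate or detection figure, so there is nothing to reproduce. The steps below only bound the effect. Episode length, rate of fall, alarm sensitivity, lag and true event rate are all assumptions.

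**1. Control ABG fixed at 120 min (no step-up).** An episode of D min at random phase is sampled with probability min(1, D/120): 15/120 = 12.5%, 30/120 = 25%, 60/120 = 50%. If the CG alarm leads to detection with probability s = 0.9, the apparent CG:G ratio at equal true rates is s/(D/120):
- D = 15: 0.9/0.125 = 7.2
- D = 30: 0.9/0.25 = 3.6
- D = 60: 0.9/0.50 = 1.8

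With 90 per arm (Sample size {14}) and an assumed true rate of 10%, there are 9 episodes per arm. CG shows 9 × 0.9 = 8.1; G shows 1.1, 2.25 and 4.5. The chance of p < 0.05 with no true difference is 66%, 47% and 18%. The ratio falls below 1 only if s < D/120; for example, s = 0.7 and D = 90 gives 0.7/0.75 = 0.93.

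**2. Adding Table 1's 30-min step-up.** Assume glucose falls in a straight line from 8 to 2.5 mmol/L and returns at the same rate, unaffected by treatment. The first control ABG falls uniformly in the first 120 min; the next follows after 30 min if the value is below 5.5, otherwise after 120 min.

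| Slope (mmol/L per min) | Below 5.5 from (min) | Below 3.0 (min) | First-ABG times that lead to detection | G detects |
|---|---|---|---|---|
| 0.03 | 83.3 | 166.7–200 | all except 80–83.3 | 116.7/120 = 97% |
| 0.05 | 50 | 100–120 | 50–60, 70–90, 100–120 | 50/120 = 42% |
| 0.10 | 25 | 50–60 | 25–30, 50–60 | 15/120 = 12.5% |

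**3. CG under the same falls.** Take the 6.1 trigger, 5-min readings (Background {6a}) and an assumed 10-min lag. For the two slower falls, repeat ABG every 5, 15 or 30 min always lands below 3.0: 100%. For the fastest fall, true glucose reaches 6.1 at 19 min, so the alarm first shows at 29–34 min. Repeats 15 and 30 min later land at 44–49 and 59–64; only 59–60 lies in the 50–60 window, so detection by ABG is 1/5 = 20%. Repeats every 5 min always hit a 10-min window: 100%.

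**4. Apparent CG:G ratio at equal true rates.** Slow fall: 1/0.97 = 1.03. Middle: 1/0.42 = 2.4. Fast: 0.20/0.125 = 1.6 up to 1/0.125 = 8. The protocol does not say how soon ABG is repeated while the alarm continues. Counting displayed CGM values as evidence would move CG towards the upper end.

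**The case against.** The strongest reply has four parts.

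- **The secondary outcomes may already use a common source.** Blood glucose management puts CGM on both groups, and the primary outcome is read from it, so mean glucose and event rates may be intended to come from the same trace. This stands. A reader might infer that they are ABG-based, but the document does not say so: the data collection list in section {18a} names blood glucose without a source and ABG only as a number of checks. An article may leave that detail to the full protocol. Only a conditional statement is justified: if ABG values were used, these outcomes would be distorted in the same way.
- **The control schedule adapts.** This also stands. A reader might take a fixed two- to fourfold excess from the 2-h interval, but that ignores Table 1. The step-up nearly removes the gap for slow falls. It starts only from a value already measured as low, so it does little for fast ones.
- **No comparison of SAEs is stated.** Secondary outcomes says SAE incidence evaluates safety; the explicit two-group wording is attached to the postoperative outcomes. That is fair, but incidence in a randomised trial will be read by arm. Cardiac arrest and death, also listed as SAEs, are not found by glucose sampling and are outside this point.
- **CGM accuracy is itself under test.** Lag or poor low-range accuracy could weaken the alarm's advantage. This is why the direction is only probable.

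A reader might also infer that events are visible only through ABG in both arms. That is true of G; in CG the CGM value is visible too, which widens the difference.

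**Conclusion.** The point holds for glucose-defined adverse reactions and SAEs recorded by investigators during surgery. Unequal detection follows from the blinding and testing rules as written, and section {6b} concedes that control monitoring misses disorders. A between-arm comparison of these events is biased, probably against CGM provided its alarm is reasonably sensitive; the alarm limits stated (6.1 or 7.8 mmol/L) lie well above 3.0.

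The size cannot be derived from the document. In the assumed scenarios with the step-up, the apparent ratio runs from about 1.03 to 8, and the top of that range needs fast falls and prompt repeat ABG. The scenarios ignore treatment given after a low reading. The coefficient of variation is unaffected, because it comes from CGM in both arms.

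**What to change.** State that hypo- and hyperglycaemic events, episodes below 3.0 mmol/L and mean glucose are compared between arms from the CGM trace in both arms, from incision to end of suture as for the primary outcome. Use one event definition, and read the blinded G trace after surgery. With the same instrument and rule in each arm, intensity of observation no longer drives the contrast.

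Report ABG-confirmed episodes, the number of ABG tests per arm and investigator-reported SAEs separately. Say that their detection differs by arm and that they are not the basis of a comparative safety claim.

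The fix needs the control trace, so reconcile the sections first. Intervention description {11a} has CGM in both groups, whereas Study setting {9} gives control ABG without CGM and Anesthesia management describes probe placement for CG only. The lower CGM trigger (6.1 in {11a}, 7.8 in {6b}, {11c} and {11d}) also needs reconciling, since it governs detection in CG.

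The cost is wording and a modest amount of analysis: the primary outcome already requires these traces, and nothing in patient management changes. The drawback is that CGM may lag or be inaccurate in the low range, which is why the ABG-confirmed counts belong beside it.
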